## Methods

### Ethical approval

Approval for the study (Code 2017–00543) was granted by the intercantonal ethics committee responsible for research at the University of Basel, the Ethikkommission Nordwestschweiz. Any protocol modifications will be communicated to this organisation and the trial sponsor, and registered on ClinicalTrials.gov.

### Study design

This study is a randomised controlled trial involving three conditions: moderate exercise, intense exercise, and rest. Alcohol-dependent, cocaine-dependent and healthy control subjects will undergo all three conditions in randomised order. The order will be determined using a computer-generated ordering system. The random sequence was generated by the web-based Research Randomizer (randomizer.org), which yielded 60 permutations of the order of sessions (rest, moderate exercise, intense exercise). These permutations were printed, placed in separate envelopes and given to a colleague not involved in the study to distribute upon recruitment of each participant. Due to the nature of the intervention, blinding will not take place. The funder has no role in the design, analysis or interpretation of the study.

No data monitoring committee is involved in this study as the intervention (exercise) is not untested or high risk, and as only two acute sessions are involved any adverse events will be addressed immediately by the investigative team. The study therefore meets the criteria of “non-critical indications where patients are treated for a relatively short time and the drugs [in this case, exercise] under investigation are well characterized and known for not harming patients” [41].

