### Participants

Twenty alcohol-dependent, 20 cocaine-dependent and 20 healthy control individuals will be recruited to take part in the study (for power calculation, please see “Statistics”). Patients from the inpatient and outpatient branches of the clinic will be informed about the study by physicians, fliers and, in the case of the inpatient clinic, periodic visits from the investigators. All individuals receiving treatment for one of the substance use disorders in question will be approached, in order to ensure that as many individuals as possible who fit the inclusion criteria are reached. The mean age and gender distribution of the cocaine-dependent and alcohol-dependent participants combined will be used as a guide for finding matched healthy controls. Alcohol-dependent and cocaine-dependent individuals will be recruited from the University Psychiatric Clinic of the University of Basel.

Inclusion criteria for these individuals are: age between 18 and 75 years; meeting three or more of the DSM-IV criteria for substance dependence (as determined by the treating physician); minimum of 20 days and maximum of 40 days abstinence from substance of dependence; able to understand and complete the informed consent; able to travel to study site independently, as confirmed by the treating psychiatrist; assessed for physical and mental fitness by the treating physician; and cleared to take part in the study.

The healthy control group will be recruited through personal contacts (the friends and family members of the investigative team and other employees of the Department for Sport, Exercise and Health) and matched for age and gender. Inclusion criteria for the healthy control group are: age between 18 and 75 years; fewer than 3 h of physical exercise or sport per week; and no history of problematic alcohol or illicit drug consumption. All participants will receive a written document outlining the requirements of the study, and informing them that withdrawal at any point will not adversely affect their medical treatment. Participants who agree with the terms will sign the adjacent consent form in the presence of a member of the investigative team, who can also answer any questions arising during the consent process.

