### Experimental conditions

To estimate the maximal heart rate of each participant, the algorithm 211 – (0.64 × age) will be used [57].

All participants will undergo three conditions, on three separate days, in a counterbalanced order. The days on which participants participate will be separated by 2–4 days. All sessions will take place in the same laboratory room at the Department of Sport, Exercise and Health at the University of Basel. Trained members of the investigative team will oversee all conditions. Owing to the nature of the intervention, investigators will not be blinded to the conditions.

The reading condition serves as a resting state comparison. Subjects will be asked to read an article about architecture in Basel. The article is 13 pages long, excluding references.

The moderate exercise condition requires participants to train on a cycle ergometer at between 50 and 60% of their maximal heart rate. Participants will wear a heart rate monitor, which will be constantly observed by study personnel, to ensure that they exercise with the correct intensity. If the participant exceeds or fails to meet the appropriate intensity, prompts will be given. Prompts will not be recorded. This constitutes a moderate, aerobic exercise bout. The exercise will last 20 min.

The intensive exercise condition is identical to the moderate condition, but participants will exercise at a pulse of between 70 and 80% of their maximal heart rate, constituting a bout approximately at the anaerobic threshold.

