### Statistics

Sample size is calculated a priori using G*Power 3.1 [58]. Based on effect sizes reported in previous studies [25, 40] and an alpha level set to 0.05, the initial power analysis indicates that 17 participants per group are required to reach 85% statistical power. As drop-outs have to be expected, the sample size is increased to 20 participants per group. Note that the power analysis is based on the acute effects of moderate aerobic exercise on prefrontal cortex activity and inhibitory control. The statistical analysis of collected data is performed with SPSS 23.0 (IBM Statistics, USA) for Windows. Acute effects of exercise on inhibitory control and HbO_2_ concentration are examined using a 2 (group: alcohol dependent, healthy controls) × 3 (condition: control, moderate exercise, highly intense exercise) × 2 (time: pre, post) ANOVA on reaction time and the haemodynamic response to incompatible trials of the Stroop colour–word test. Additionally, effects of exercise on cue-elicited craving and HbO_2_ concentration (neutral cues subtracted from alcohol/cocaine cues) are investigated by applying a 2 (group) × 3 (condition) × 2 (time) ANOVA. Main effects and interactions are reported. Subsequently, Bonferroni-corrected *t* tests are used to decompose any significant interactions. The level of statistical significance is set to *p* < 0.05. Data from participants who do not complete all three measurement points will not be used.

Regarding missing data, as participants who do not complete all three sessions will be excluded from the study, it is anticipated that missing data will chiefly be due to faults in the fNIRS and Stroop programming, and thus will be missing at random. For this reason, multiple imputation will be used to address this issue.

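### The randomisation procedure described does not ensure, within a group of 20, the counterbalanced session order that the protocol states

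*Protocol article*

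**What the plan says.** Two sections of the protocol article describe the order of sessions differently.

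- **Study design**: "Alcohol-dependent, cocaine-dependent and healthy control subjects will undergo all three conditions in randomised order". The mechanism follows: "The random sequence was generated by the web-based Research Randomizer (randomizer.org", "which yielded 60 permutations of the order of sessions (rest, moderate exercise, intense exercise". The orders were printed, placed in separate envelopes and "given to a colleague not involved in the study to distribute upon recruitment of each participant". No block, Latin square or other balance constraint is mentioned, and no separate set of envelopes for each group.
- **Experimental conditions**: "All participants will undergo three conditions, on three separate days, in a counterbalanced order".

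The Participants section sets the sizes: "Twenty alcohol-dependent, 20 cocaine-dependent and 20 healthy control individuals will be recruited". The Statistics section gives a group × condition × time ANOVA with no session or sequence term, and uses only participants who complete all three sessions. The Abstract places the Stroop test and the film before and after every condition. The cue exposure section adds that the same film block is used each time.

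**The concern.** Counterbalancing is a design property: each order, and so each condition in each session position, occurs equally often or as nearly so as the numbers allow. The article uses the same word for the first Stroop block type, so it is not a loose synonym for random. A list of random orders gives balance only on average over hypothetical repetitions, not in the 20 people actually enrolled in a group.

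This matters here because the film and the Stroop test each recur six times. Measuring before and after each condition removes stable differences between days. It does not remove practice or habituation that makes the pre-to-post change itself depend on session number. If one condition falls in session 1 more often than another, the comparison of conditions picks up part of that effect. If the imbalance differs between groups, the group × condition × time interaction picks it up too. The listed ANOVA has no term to absorb it.

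**Working it through.** **Plan's own figures.** 3 groups × 20 = 60 orders, which agrees. Three conditions have only 3! = 6 distinct orders, so the list is 60 draws from six. "the initial power analysis indicates that 17 participants per group are required to reach 85% statistical power" and "As drop-outs have to be expected, the sample size is increased to 20 participants per group": 17/(1 − 0.15) = 20, which agrees with an implied 15% drop-out. The 17 itself cannot be reproduced because no effect size is given, but nothing below depends on it.

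**Best attainable balance.** 20/6 = 3.33, so exact balance is impossible under any scheme. The best split is four orders used 3 times and two used 4 times.

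**Probability of the best split in one group of 20**

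- Independent draws: C(6,2) × 20! / (3!⁴ × 4!²) / 6²⁰ = 0.0134. For all three groups: 0.0134³ = 2.4 × 10⁻⁶. For at least one: 1 − (1 − 0.0134)³ = 4.0%.
- List of 60 with exactly 10 of each order, shared by the groups: C(6,2) × C(10,3)⁴ × C(10,4)² / C(60,20) = 15 × 120⁴ × 210² / (4.19 × 10¹⁵) = 0.033.

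**Typical imbalance under independent draws (simulation)**

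| Event | One group of 20 | At least one of three groups |
|---|---|---|
| An order is never used | 15% | 1 − 0.85³ = 39% |
| First-session counts of the conditions differ by 6 or more | 29% | 1 − 0.71³ = 64% |

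With blocks of six per group, first-session counts never differ by more than 2.

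**Size of the chance error.** The documents give no practice effect. *Assumption:* the pre-to-post practice gain is 0.4, 0.1 and 0 SD in sessions 1, 2 and 3. For one participant, the practice part of moderate minus rest takes the values ±0.3, ±0.4 and ±0.1, each with probability 1/6.

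- Variance per participant: 2 × (0.09 + 0.16 + 0.01)/6 = 0.0867, so SD = 0.294.
- Independent draws, n = 20: 0.294/√20 = 0.066. For n = 17: 0.294/√17 = 0.071.
- Balanced list of 60 shared by the groups, n = 20: 0.066 × √(40/59) = 0.054.
- Blocks of six per group, n = 20: the 18 participants in complete blocks cancel. The other two give √(2 × 0.0867 × 4/5)/20 = 0.372/20 = 0.019.
- Blocks of six, 17 random completers of 20: the variance of the 20-person mean is 0.019² ≈ 0.00035. Random loss of three adds about (0.0909/17) × (3/20) = 0.00080, where 0.0909 is the variance among the 20 with divisor 19. √0.00115 = 0.034.
- Difference between two groups of 20, independent draws: √2 × 0.066 = 0.093. With blocks per group: √2 × 0.019 = 0.026.

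**Against sampling error.** *Assumption:* the paired contrast has residual SD 1. The SD of the estimate for n = 20 is then 1/√20 = 0.224 without order effects and √(1 + 0.0867)/√20 = 0.233 with them, an increase of about 4%.

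**The case against.** The strongest reply has four parts.

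1. **The text is silent rather than explicit.** A reader might infer that the list was unrestricted and drawn on by all groups from one pile. The article says neither. Sixty is 3 × 20 and also 6 × 10, so a balanced list or envelopes sorted by group is not excluded, and a condensed article may omit such detail. This stands. The supportable statement is that the described procedure does not ensure balance.
2. **Some balance may occur by chance.** A reader might conclude that no group is counterbalanced. That goes too far: even with independent draws, at least one group reaches the best split with probability 4%.
3. **Random order is valid.** A reader might take the imbalance as bias. Independent random ordering is unbiased in expectation, and the extra variation enters the within-participant error. A simulated paired t test under the same assumptions kept its type I error at 0.050. This stands, and it limits the harm to a modest loss of precision.
4. **The practice gain is assumed, and drop-out erodes blocking.** The protocol includes practice trials to limit learning. With 17 completers the advantage of blocking is about twofold (0.071/0.034 = 2.1), not the 3.5-fold seen with all 20 (0.066/0.019). Both points stand.

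What the reply does not remove is the mismatch. The article describes generation, printing, enveloping and distribution, and those steps do not support the word used in Experimental conditions. Even the generous reading of an overall balanced list shared by the groups gives the best split in only about 3% of groups. Only a list balanced within each group would secure the stated property, and none is described.

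**Conclusion.** The point holds as a mismatch between a stated design property and the stated procedure. If orders were drawn independently, a group of 20 reaches the best attainable balance with a probability of about 1%. If the list was balanced overall but shared, the probability is about 3%. If the list was in fact blocked by group, the procedure is sound and only its description needs completing.

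The consequence is avoidable chance error, not bias. Under the assumed 0.4/0.1/0 SD practice gain its SD is 0.066 for 20 participants and about 0.071 for 17 completers, against 0.019 and 0.034 with blocks per group. With a residual SD of 1, this widens the standard error by about 4%. A smaller practice gain shrinks these figures in proportion, and a larger one raises them. The change is worth making because it is nearly free, not because the trial's validity depends on it.

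**What to change.** - State in Study design whether the list was blocked and whether each group had its own list.
- If it was not blocked by group, regenerate the unused envelopes as three lists, one per group, in permuted blocks containing each of the six orders once. The same uninvolved colleague can hold them. Amend Study design and report how orders were generated before and after the change.
- If the list cannot be changed, replace 'counterbalanced' with 'randomised' in Experimental conditions.
- In either case, add session number to the model so that it acts on the pre-to-post change (session and session × time), and report order counts per group among those recruited and those analysed.

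**Cost:** a new set of envelopes and a few sentences. The downside is that two generation procedures must be reported for one trial. The article says only that recruitment is incomplete, so the number of unused envelopes is unknown. The fewer remain, the less blocking gains, and the more the session term and the order counts matter. The session term uses a few degrees of freedom.

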**Outcomes:**

The primary outcome measures are self-reported craving, inhibitory control and cerebral haemodynamic response to the Stroop test and a substance-related film. It is hoped that the findings from this study will shed more light on the role of exercise in the treatment of substance use disorders, particularly its scope in preventing relapse through reduced craving severity.

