Participants will receive a financial incentive of 150 CHF for completion of all three measurements periods, and travel costs will be refunded. Participants will continue to receive treatment as usual during the study phase. In order to optimise participant retention, participants will be contacted by telephone if any of the three scheduled sessions are missed, in order to ascertain, if possible, whether a new session can be scheduled or whether the participant wishes to cease their involvement in the study. Participants may also request telephone or text message reminders of their scheduled sessions.

Prior to the baseline session, all participants will undergo a resting echocardiogram on arrival at the test laboratory. Any participants with questionable findings will be excluded from further participation and referred to their treating physician. Further exclusion criteria include: illness during the study period; inability to complete either exercise condition; and failure to attend three sessions at a maximum of 4 days apart. Participants are not prohibited from any activities during the trial. Any adverse events occurring during the trial will be documented, submitted to the treating physician and ethical committee, and may, upon discussion with the treating physician, lead to exclusion of the participant from the trial.

Data for all participants will be stored only at the intervention site, in coded form, with the key only available to the onsite investigative team. No data from participants who do not complete the full study will be retained or analysed. A single member of the team is responsible for coding, and the code key is locked in a single office at the investigation site. Data entered electronically are not linked in any way to this code list; hard copies of questionnaires are stored in a separate archive. Data entry will be controlled by the principal investigator following entry by other investigators, comparing hard copies with electronic records. Following the trial, archived material will be kept for 10 years, in line with the requirements of the local ethics committee. An inventory of each section of the trial is visible in the SPIRIT checklist (Additional file 1).

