### fNIRS recordings

Using fNIRS (NIRSport, NIRx Medizintechnik GmbH, Germany), cerebral oxygenation is recorded during the inhibitory control task and alcohol cue exposure. Probes are applied using a flexible cap adjustable to the participant’s head size. Light sources and detectors are placed over the prefrontal region using the Fz position of the EEG as reference. Channel distances are fixed to 35 mm to allow measurements at equal depths. Offline processing of the collected data is performed with Homer 2 [54] and includes the following steps: removal of discontinuities, artefact rejection and correction using spline interpolation, band-pass filtering (0.01–0.2 Hz), conversion into haemodynamic states using the modified Beer–Lambert Law [55] and normalisation using the pre-task period as baseline. As findings of a review have indicated widespread prefrontal cortex hypoactivation during inhibitory control tasks and hyperactivation during the presentation of drug-related cues, cerebral oxygenation is examined across channels placed over the prefrontal region [7].

HbO_2_ is calculated as the dependent variable, because Strangman et al. [56] have shown high correlations between this parameter and the blood oxygen level. For the assessment of cue-elicited craving, difference waveforms (created by subtracting the haemodynamic response to neutral cues from alcohol/cocaine cues) are extracted for statistical analysis.

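### The reason given for having no blinding does not reach the offline fNIRS processing, which could be done on files masked for condition and time point

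*Protocol article*

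**What the plan says.** Two places in the Methods address blinding. Study design, directly after the allocation procedure, states "Due to the nature of the intervention, blinding will not take place". Experimental conditions, after saying that trained team members oversee the sessions, states "Owing to the nature of the intervention, investigators will not be blinded to the conditions". Both give the same reason, and neither makes an exception for data processing or analysis.

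The fNIRS recordings section says "Offline processing of the collected data is performed with Homer 2", and lists among the steps "removal of discontinuities, artefact rejection and correction using spline interpolation", followed by filtering, conversion to haemodynamic quantities and baseline normalisation. It does not say whether the artefact steps are manual or automated, or who carries them out.

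The abstract places the fNIRS signal among the primary outcomes: "The primary outcome measures are self-reported craving, inhibitory control and cerebral haemodynamic response to the Stroop test and a substance-related film".

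The Participants section describes coded data storage, with the key held by the on-site team: "A single member of the team is responsible for coding". This is described as a confidentiality arrangement. Nothing there says that condition or time point is hidden from anyone.

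**The concern.** Exercise cannot be hidden from the person cycling or from the person watching the heart-rate monitor. It can be hidden from someone who later opens a recording on a computer. The plan gives a reason that applies to the first two people and draws from it a statement that, as worded, also covers the third.

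This matters because the processing decides which parts of the signal enter the analysis and which are corrected. The outcome is primary, and the expected direction for each session is written down. If the operator has any discretion and can see the labels, decisions on borderline segments could lean towards the hypotheses without any intent to do so. Such a lean would be differential between conditions, so neither the crossover design nor the ANOVA would remove it.

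**Working it through.** No arithmetic applies; the question is whether the stated reason covers the step. Taking the passages in turn:

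1. **Reach of the statement.** Study design is unqualified. Experimental conditions names investigators in general. Read literally, the two together include anyone on the team who processes data.

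2. **Reach of the reason.** The nature of the intervention is visible only during a session. The fNIRS recordings section places processing after data collection. A file can be renamed between recording and processing, so the reason does not extend to this step.

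3. **Can the step change the result?** Artefact rejection removes data, and spline correction alters data. Both act on HbO2, which the Statistics section analyses for incompatible Stroop trials and for the cue-minus-neutral difference. They can change the result if they involve choice. The article does not settle whether they do.

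4. **Would the operator know the expected direction?** The hypotheses in the Background give, relative to rest:

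| fNIRS outcome | After moderate exercise | After intense exercise |
|---|---|---|
| Stroop test | more prefrontal activity | less prefrontal activity |
| Substance cues | less prefrontal activity | no difference |

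The prediction differs by intensity in both rows and is opposite in the first. A condition label and a pre/post label together reveal what each file is expected to show.

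5. **Does anything else in the article supply masking?** The coded storage in the Participants section protects identity, and the team holds the key. It does not mask condition.

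6. **Consequence for missing data.** The Statistics section expects gaps to come chiefly from equipment and programming faults, and on that ground treats them as missing at random and plans multiple imputation. That justification does not cover data removed by an operator who was influenced by both the label and the look of the signal. The imputation would then rest on a weaker footing.

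**Size.** The article gives no rejection criterion, no expected rejection rate and no effect size, so no shift in the contrasts can be derived from it.

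**The case against.** The strongest reply is that both sentences are routine disclosures. One follows the allocation procedure and the other follows the supervision of sessions. On that reading the article is merely silent on masked processing, and a condensed article may leave this to the full protocol. This has some force: the authors may never have meant to rule out masked processing. But the statements are affirmative, carry a reason and admit no exception, so the wording is broader than the reason even if the intention was narrower.

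Four stronger readings are tempting, and the document does not support them:

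- **That rejection is judgement-based.** The article lists a processing sequence in named software and does not say that a person decides channel by channel. If the steps are automated with settings fixed in advance, the risk is smaller. The article also examines the signal across the prefrontal channels rather than at selected ones, which narrows discretion.
- **That post-exercise recordings need more rejection.** Recordings are made before and after the bout, not while cycling, and the Background describes fNIRS as relatively robust to movement. The Discussion mentions systemic blood-flow changes as a problem of interpretation, not as a cause of more rejection.
- **That the Stroop performance data are equally exposed.** The test is computer-administered, accuracy and reaction time are calculated from the responses, and no discretionary rejection step is described.
- **That the bias can be expressed as a share of the detectable effect.** This would need an assumed shift with no source in the article. It would also need an effect size, test family and correlation that the article does not state for its power calculation.

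**Conclusion.** The point holds in a limited form. The no-blinding statement is wider than its stated reason, and the step it wrongly takes in is the offline fNIRS processing of a primary outcome with condition-specific predictions. The possible harm is differential error in the fNIRS contrasts. It depends on one assumption that the article neither confirms nor excludes: that at least one rejection or correction step involves operator choice. No bias is demonstrated, and its size is not estimable from the document. Self-reported craving cannot be masked in this design and is outside the point, as are the computer-recorded Stroop scores. This is an inexpensive improvement to a stated design choice, not a flaw that invalidates the trial.

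**What to change.** Reword Study design and Experimental conditions so that the absence of blinding applies to participants and session staff. Then add to the fNIRS recordings section that:

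- a team member who does not process the recordings relabels the files so that condition and pre/post are hidden; the person already responsible for coding could do this, provided that person is not also the processor and the processor has no access to the key in the meantime;
- settings for artefact rejection and correction are fixed in advance;
- processing of all files is completed and the processed data frozen before labels are restored.

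The cost is the file relabelling, a few sentences and a short delay before labelled data can be analysed. Sessions, assessments and sample size are unchanged, and the article reports recruitment as incomplete, so the change could still be made at that stage. Masking may be imperfect, because exercise-related systemic changes could remain visible in the signal; fixing the settings in advance is therefore needed as well as the relabelling.
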